## 9 Statistical Analyses/Methods

### 9.1 Blinded Data Review Meeting

Given the aggregated nature of the data, no blinded data review is performed.

### 9.2 Subject Disposition

There will be a clear accounting of all sites that participated in the study using tables and figures. The number of sites which were randomized, and that entered and completed each phase of the study will be provided as well as the reasons for all post-registration discontinuations. A flow chart according to the CONSORT statement will be prepared. The number of patients being admitted to the site and screened for multidrug-resistant organisms will be added.

A description of the cohort will be given using baseline characteristics.

### 9.3 Analysis of Primary Outcome Variables

Based on previous data, we assume a correlation within sites and phases of maximally 0.01. Given that the previously observed correlation is very low, the time lag between the two trial phases is long and different patients are included in the two trial phases at each site, no carry-over effects are assumed. We thus are not expecting that effects of one treatment phase would influence the second period after cross-over, so that data from two phases at one site are regarded as independent.

For the primary analysis, we estimate a GEE model, taking a possible correlation within the phases at one site (cluster as defined above) into account. Assuming a very low intra-cluster correlation, we use the independence structure for the working correlation. To obtain an estimate of the risk difference, an identity link is used. To test for non-inferiority, a margin of 0.05 has been defined.

|                         |                                                                                                                                         |
|-------------------------|-----------------------------------------------------------------------------------------------------------------------------------------|
| Outcome variable        | Anzahl_gramNeg_nurLOS, Anzahl_gramNeg_nurLOS_negativ                                                                                    |
| Endpoint                | Gram-negative BSI                                                                                                                       |
| Effect measure          | Risk difference                                                                                                                         |
| Primary Estimand |                                                                                                                                         |
| Population              | Newborns requiring intensive care in one of the participating NICUs undergoing KRINKO screening and being treated with hygiene measures |
| Treatment               | Standard hygiene measures (hand disinfection plus gloves and gowns, CO) versus hand disinfection only (IV)                              |
| Hypothesis              | Non-inferiority, i.e.
$H_0$ : Risk for gram-negative BSI in IV – Risk for gram-negative BSI in CO group $\geq 0.05$                  |

|                                                  |                                                                                                                                                                                                                                                                                                                                                                                                                                                                                                                                                                                                                                                                                                                                                                                                                                                                                                                                                     |
|--------------------------------------------------|-----------------------------------------------------------------------------------------------------------------------------------------------------------------------------------------------------------------------------------------------------------------------------------------------------------------------------------------------------------------------------------------------------------------------------------------------------------------------------------------------------------------------------------------------------------------------------------------------------------------------------------------------------------------------------------------------------------------------------------------------------------------------------------------------------------------------------------------------------------------------------------------------------------------------------------------------------|
|                                                  | $H_1$ : Risk for gram-negative BSI in intervention group – Risk for gram-negative BSI in control group < 0.05                                                                                                                                                                                                                                                                                                                                                                                                                                                                                                                                                                                                                                                                                                                                                                                                                                       |
| Significance level                               | 0.05 (one-sided)                                                                                                                                                                                                                                                                                                                                                                                                                                                                                                                                                                                                                                                                                                                                                                                                                                                                                                                                    |
| Intercurrent Events                              | None                                                                                                                                                                                                                                                                                                                                                                                                                                                                                                                                                                                                                                                                                                                                                                                                                                                                                                                                                |
| Strategy                                         | n.a.                                                                                                                                                                                                                                                                                                                                                                                                                                                                                                                                                                                                                                                                                                                                                                                                                                                                                                                                                |
| Adjustments for covariates                       | None                                                                                                                                                                                                                                                                                                                                                                                                                                                                                                                                                                                                                                                                                                                                                                                                                                                                                                                                                |
| Main estimator                                   | 
Risk difference is estimated from a GEE logistic regression model with identity link using the following command from the R-library geepack:
 <pre>geeglm(cbind(Anzahl_gramNeg_nurLOS, Anzahl_gramNeg_nurLOS_negativ) ~ Randomisierung, family = binomial(link = "identity"), id = Cluster, corstr = "independence")</pre> 
with the variable <code>Randomisierung</code> indicating the phase (CO vs. IV)
 
From this model, the 95% confidence interval for the risk difference and the one-sided p-value are estimated.
                                                                                                                                                                                                                                                                                                                                                                                                         |
| Missing data                                     | Analyses are based on complete cases                                                                                                                                                                                                                                                                                                                                                                                                                                                                                                                                                                                                                                                                                                                                                                                                                                                                                                                |
| Interpretation for the primary estimand          | If non-inferiority is statistically significant it is shown that newborns requiring intensive care being treated in a NICU with a hand disinfection only-protocol do not have a higher risk of gram-negative infections than corresponding newborns treated in a NICU with a standard protocol.                                                                                                                                                                                                                                                                                                                                                                                                                                                                                                                                                                                                                                                     |
| Interim analysis                          | n.a.                                                                                                                                                                                                                                                                                                                                                                                                                                                                                                                                                                                                                                                                                                                                                                                                                                                                                                                                                |
| Sensitivity analyses: logistic regression | 
As sensitivity analysis, a logistic regression model is estimated assuming independence of the observations within one phase at one site using the following R-command:
 <pre>glm(gramNeg_nurLOS ~ Randomisierung, family = binomial(link = "identity"))</pre> 
with the variable <code>Randomisierung</code> indicating the phase (CO vs. IV)
 
From this, the one-sided descriptive p-value and the 95% confidence interval are estimated.
                                                                                                                                                                                                                                                                                                                                                                                                                                                                                       |
| Hypothesis                                       | n.a.                                                                                                                                                                                                                                                                                                                                                                                                                                                                                                                                                                                                                                                                                                                                                                                                                                                                                                                                                |
| Significance level                               | Descriptive analysis only                                                                                                                                                                                                                                                                                                                                                                                                                                                                                                                                                                                                                                                                                                                                                                                                                                                                                                                           |
| Sensitivity analyses: Confounding         | 
As further sensitivity analyses, the same models are estimated as above with simultaneously taking possible confounders into account:
 <pre>geeglm(cbind(Anzahl_gramNeg_nurLOS, Anzahl_gramNeg_nurLOS_negativ) ~ Randomisierung + Confounder, family = binomial(link = "identity"), id = Cluster, corstr = "independence")</pre> 
with the variable <code>Randomisierung</code> indicating the phase (CO vs. IV) and <code>Confounder</code> being one of the three variables
 
 
• Percentage of shifts with understaffing in the month [<code>GBA_Prozent</code>]
 
• Count of days with blocked beds in the month [<code>Tage_Bettensperrung</code>]
 
• additional workload in the NICU by patients > 28 days of age [<code>Aufnahme_Päd</code>].
 
 
The risk difference with regard to the intervention is estimated accordingly with 95% confidence intervals.
 |
| Hypothesis                                       | n.a.                                                                                                                                                                                                                                                                                                                                                                                                                                                                                                                                                                                                                                                                                                                                                                                                                                                                                                                                                |
| Significance level                               | Descriptive analysis only                                                                                                                                                                                                                                                                                                                                                                                                                                                                                                                                                                                                                                                                                                                                                                                                                                                                                                                           |
| Supplementary analysis                    | n.a.                                                                                                                                                                                                                                                                                                                                                                                                                                                                                                                                                                                                                                                                                                                                                                                                                                                                                                                                                |
| Subgroup analysis                         | n.a.                                                                                                                                                                                                                                                                                                                                                                                                                                                                                                                                                                                                                                                                                                                                                                                                                                                                                                                                                |

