**Statistical power:** We plan with 12 sites in 2 phases (intervention and control phase). At least 18 patients per site and phase in 12 sites will be required, thus  $n=432$  in total; accounting for a patient drop-out of maximally 10%, 480 patients need to be included in total. Collecting data over 12 months per phase ensures inclusion of a sufficient number. Estimation of infection risk differences between intervention and control phases will be performed using generalized estimating equations (GEE) models for binary endpoints with identity link; test of non-inferiority with margin of 0.05 using one-sided significance level of 0.05

**Conclusions:** BALTIC should contribute to better evidence on the effectiveness of hand disinfection and extended barrier precautions in critically ill newborns. Further benefits include comprehensive multi-center data collection on MDRO colonization dynamics, an improved awareness on IPC strategies and establishment of network platforms including antimicrobial stewardship programs.

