## **Trial design**

In the participating centers, all newborns requiring intensive care undergo colonization screening based on KRINKO recommendations. If a 2MRGN positive pathogen is detected this infant is treated with hygiene measures as described in the intervention (focus on standard hand disinfection) or control procedure (standard hand disinfection plus barrier precautions), depending on the randomization of the center. The study has been conducted in a cross-over design with a change between the intervention and control group after 12 months. All other patients (screening negative or positive for a pathogen included in the KRINKO recommendations apart from 2MRGN) receive the standard care based on screening results and local guideline. After 6, 12, 18 and 24 months, the compliance will be evaluated by the means of random observations of hygiene in the NICU in collaboration with local institutions for hospital hygiene followed by standardized training modules. The PICO question of this multicenter, cluster RCT with cross over is whether in the **Population** of preterm infants and critically ill neonates requiring intensive care who are colonized with 2MRGN the **Intervention** ***standard hand hygiene disinfection*** is non-inferior to the current KRINKO recommendation (**Control**) of ***standard hand hygiene disinfection + barrier precautions (gloves/gown)*** for the **Outcome** overall rate of HA Gram-negative bloodstream infections (primary endpoint).

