### *Outcomes*

The primary endpoint is the rate of HA bloodstream infections with Gram-negative pathogens in all preterm and newborn infants who received colonization screening. This outcome is defined clinically according to NEO-KISS criteria (at least two clinical signs of sepsis + one laboratory sign, e.g. increase in C-reactive protein > 10mg/l) after 72 hours of life and requires the detection of a Gram-negative pathogen in the blood culture. Blood-culture isolates will be sent from the study centers to the study management.

Key secondary endpoint is the 2MRGN transmission rate which is assumed if another infant is colonized with the same 2MRGN pathogen after 2MRGN colonization or infection of an infant

requiring intensive care in a temporal (maximum 90 days) and spatial context (potential contact in the intensive care unit) (26). This assumption is made if, in addition to pathogen identification, the antimicrobial susceptibility testing patterns are identical. Suspected transmission of or bloodstream infection with an 2MRGN pathogen will be reported to the study management as severe adverse event within 24 hours.

Transmission/outbreak management remains the responsibility of the local interdisciplinary infection control team and is carried out according to local standards, including the decision whether to initiate genetic identity testing in the acute situation. 2MRGN isolates will be shipped from local sites and molecular typing will be performed at the Department of Infectious Diseases and Medical Microbiology at the University of Lübeck. Other secondary outcomes at the level of study sites per period ("study phase") are:

- Rate of clinical and culture proven infections
- Rate of infection outbreaks
- Number of initiated antibiotic cycles
- Duration of antibiotic treatment (days)
- Exposure to reserve antibiotics, including Carbapenems per study site in % infants.

To assure documentation of relevant outcomes, intensive interdisciplinary collaboration (neonatology/infectiology/hygiene/pharmacy/management) is required. Data are collected by monthly cluster report forms on infection and transmission rates and yearly surveillance of antibiotic use, disinfectant consumption, and cost estimations.

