#### *Sample size calculation and statistical analysis*

GNN and PRIMAL centers treat on average 150 preterm and critically ill neonates per year with compulsory colonization screening. The center-specific rates of Gram-negative HA infection ranges between 1.5 and 6%. Based on single center data as described above and other cohort studies (20-22) we expect 10% of these infants to be colonized with 2MRGN during hospital stay, i.e. 180 infants per 12 months observational period.

Based on previous data, we assume an intracluster correlation of maximally 0.01. Given that the observed correlation is very low, the time lag between the two trial periods is long and different patients are included in the two trial periods at each site. No carry-over effects are assumed, as we are not expecting that effects of one treatment period would influence the second period (after cross-over) since medical care-givers are aware of the study period they are in. Data from two periods at one site are regarded as two independent sites. We further assume a frequency of Gram-negative HA infections in the controls of 3% and a non-inferiority limit of 5%. Striving for a power of 0.8 ( $1-\beta$ ) with a one-sided significance level  $\alpha$  of 0.05, at least  $n=18$  patients per site and phase are required for analysis with 12 sites, thus  $n=432$  in total. To allow for a maximal drop-out of 10% drop-out, at least 480 patients need to be included.

The primary data analysis will be performed according to the intention-to-treat principle (non-linear mixed effect regression models, logit link). Generalized estimating equations are performed to determine the infection rates between the two regimens. Secondary endpoints are analysed as the primary endpoint per individual or per cluster.

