## 5 Database

The database is the data taken over from the clinical project management team according to Chapter 3. In this, data is documented entirely on an aggregated level, i.e., per month per site.

The data is structured as follows:

- Every of the 12 sites participates in the study in two phases, in one of which hand disinfection alone (IV), in the other hand disinfection plus gloves and gowns is applied (CO). The order of the two phases is randomized.
- Every phase has a duration of 12 months, so that for every site, data is collected for 24 months.
- Each of the two phases at one site is considered one cluster.
- Given the aggregation of the data in months, the observational unit is the month (month-level variables).
- Some variables give the count of patients with a specific event. From this and the number of admissions in that month, the number of patients without the specific events is constructed as well as data on patient-level is constructed for analyses (patient-level variables).

To obtain the count of patients without a specific event, the number of events is subtracted from the number of admissions [Aufnahmen\_Neo] rendering the following additional variables:

| Count of patients with the event
(original variable) | Count of patients without the event
(constructed variable) |
|---------------------------------------------------------|---------------------------------------------------------------|
| Anzahl_gramNeg_nurLOS                                   | Anzahl_gramNeg_nurLOS_negativ                                 |
| Transm_Patient                                          | Transm_Patient_negativ                                        |
| Transmission_2MRGN_Patient_SAE                          | Transmission_2MRGN_Patient_SAE_negativ                        |
| Anzahl_kl_Sepsis_allg                                   | Anzahl_kl_Sepsis_allg_negativ                                 |
| Anzahl_BKpos_Sepsis_allg                                | Anzahl_BKpos_Sepsis_allg_negativ                              |
| Anzahl_2MRGN_LOS                                        | Anzahl_2MRGN_LOS_negativ                                      |

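### The hypothesis concerns 2MRGN-colonised infants, but the primary model divides by all admissions; the 0.05 margin and n=432 are tied to neither population, so a non-inferior result could not support the stated conclusion

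*Combined protocol and SAP*

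**What the plan says.** The documents describe the population in three ways.

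- **Colonised infants.** The PICO question (protocol, Trial design) is about "preterm infants and critically ill neonates requiring intensive care who are colonized with 2MRGN". The hypothesis at the end of the protocol's rationale section and the primary objective in SAP 4.1 are likewise about care of colonised infants. Under Trial design, all other infants receive the local standard in both phases.
- **Screened infants.** Protocol, Outcomes, defines the primary endpoint "in all preterm and newborn infants who received colonization screening". The primary estimand in SAP 9.3 also covers newborns undergoing screening.
- **Admissions.** SAP section 5 builds the non-events from monthly admission counts: "From this and the number of admissions in that month, the number of patients without the specific events is constructed". The primary GEE model in SAP 9.3 uses these event and non-event counts.

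One margin serves all three. SAP 9.3 says "To test for non-inferiority, a margin of 0.05 has been defined", and the synopsis specifies a "test of non-inferiority with margin of 0.05 using one-sided significance level of 0.05". The protocol's sample-size section says "we expect 10% of these infants to be colonized with 2MRGN during hospital stay, i.e. 180 infants per 12 months observational period". It then sets out the assumptions ("We further assume a frequency of Gram-negative HA infections in the controls of 3% and a non-inferiority limit of 5" per cent; "Striving for a power of 0.8") and arrives at 18 per site and phase. It does not say whether those 18 are colonised or screened infants. No section gives a reason for the margin. SAP 9.3 would read a significant result as showing that infants under hand disinfection alone have no higher risk, without mentioning the margin.

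**The concern.** A non-inferiority margin has meaning only for a named population and baseline risk. Here the question is about roughly one infant in ten, while the test is run on all of them. Three consequences follow.

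- The stated size and power do not describe the analysis that will be done.
- The margin is larger than the whole assumed control risk.
- An effect confined to the infants whose care changes is averaged over nine times as many infants whose care does not change.

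At stake is the trial's main message. A positive result could be read as evidence that gloves and gowns make no difference for colonised infants, when the analysis could not have detected a large difference in them.

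**Working it through.** **Inputs from the documents:** control risk 3%; margin 0.05; one-sided alpha 0.05; power 0.80; ICC at most 0.01; 12 sites with two phases each, so 12 clusters per regimen; 150 infants per site-year; 10% colonised. Equal cluster sizes are assumed.

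**1. The plan's own figure.** For 3% versus 3%, the Farrington-Manning score formula gives n = 182.6 per regimen before clustering. With m infants per cluster, solve 12m = n[1 + (m − 1) × 0.01]:

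m = 0.99 × 182.6 / (12 − 0.01 × 182.6) = 17.8, so 18.

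Then 18 × 24 = 432, and 432 / 0.9 = 480. Both stated figures reproduce. (The simple unpooled formula at the same alpha gives n = 144 and m = 13.5, which does not match.)

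**2. Which population is 432?**
- All infants: 12 × 150 × 2 = 3,600, which is 3,600 / 432 = 8.3 times the stated number.
- Colonised infants: 10% of 150 = 15 per site and phase against 18 required; 15 × 24 = 360, short of 432.

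**3. What the margin tolerates.** At 3% control risk, any true risk below 3% + 5% = 8%, a ratio of 8/3 = 2.67. At the ends of the protocol's centre range the ratio is 6.5/1.5 = 4.33 and 11/6 = 1.83. None of this depends on the denominator.

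**4. Chance of declaring non-inferiority.** Let

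SE = √{[p0(1 − p0) + p1(1 − p1)] × [1 + (m − 1) × ICC] / n}

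P = Φ((0.05 − (p1 − p0)) / SE − 1.645)

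| True risks | n per regimen | ICC | SE | P |
|---|---|---|---|---|
| 3% v 3% | 1,800 | 0.01 | 0.0090 | about 1.00 |
| 3% v 3% | 1,800 | 0 | 0.0057 | about 1.00 |
| 3% v 6% | 216 | 0.01 | 0.0215 | 0.24 |
| 3% v 6% | 1,800 | 0.01 | 0.0109 | 0.58 |
| 3% v 6% | 1,800 | 0 | 0.0069 | 0.90 |

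For example, the fourth row is Φ(0.02 / 0.0109 − 1.645) = 0.58. A beta-binomial simulation with a cluster-robust variance (40,000 replicates) gave 29%, 61% and 90% for the last three rows.

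**5. Largest observed risk that passes.** Holding the observed control risk at 3%, solve p1 − 0.03 + 1.645 × SE = 0.05.
- At 216 per regimen, ICC 0.01: 4.7%.
- At 1,800 per regimen: 6.2% (ICC 0.01), about 111 against 54 infections.
- At 1,800 per regimen: 6.8% (ICC 0), about 123 against 54 infections.

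If the upper limit of the two-sided 95% interval decided instead, the last two become 5.9% and 6.6%.

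**6. Dilution.** Assume the regimen affects only the colonised 10% and nothing spreads onward. Reaching the margin then needs a rise of 0.05 / 0.10 = 50 points in them. A rise from 3% to 20% gives an overall risk of 0.9 × 3% + 0.1 × 20% = 4.7%. With SE = 0.0101 (ICC 0.01), P = Φ(0.033 / 0.0101 − 1.645) = 0.95.

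**The case against.** A reader might infer that the margin and sample size were set for colonised infants and then carried over to a larger set. The documents do not show this, and some evidence points the other way. The 3% lies within the all-infant centre range of 1.5 to 6%. In the single-centre cohort, 3 of 30 colonised infants (10%) had 2MRGN sepsis. The synopsis expects 12 months per phase to yield enough infants, which fits all screened infants better than 15 colonised ones per site and phase.

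Nor did the SAP switch the population: the protocol's own endpoint already covers all screened infants. A unit-wide risk is also a legitimate target, because barrier care is meant to stop spread to other infants and whole sites are randomised. Onward transmission would soften the dilution in step 6. Admissions and screened infants may nearly coincide, since participating sites must screen on admission; the size of any gap cannot be derived from the documents. The 18 is a stated minimum, so exceeding it is not an error in itself.

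These points stand. They remove any claim about how the margin arose. They do not supply a justification for it, a population for the 432, or a basis for concluding about colonised infants from an all-admission risk difference.

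**Conclusion.** The concern holds as a mismatch between question, analysis and conclusion. The documents leave open which population the margin and the 18 per site and phase refer to, and 432 at 80% power fits neither candidate. A non-inferior result from the planned model could not support the hypothesis for colonised infants, nor the statement that risk is no higher.

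Two stronger readings should be avoided. The denominator is not what puts a doubling inside the margin: a 5-point margin on 3% contains it with any denominator. The larger set adds precision, which raises the chance that a true doubling passes from about 24% to between 58% and 90%, and it adds dilution. Nor is the test unable to fail: at ICC 0.01 a true doubling would still fail about 42% of the time.

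The figures assume 150 infants in every site and phase, a 3% control risk and a normal approximation. The 0.95 also assumes no onward transmission.

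**What to change.** 1. State in protocol and SAP that the primary population is all screened infants. Use the number screened as denominator; SAP 9.2 already plans to report it. Replace the 432 and 80% statement with the expected size and precision for that set: about 3,600 infants, SE about 0.006 (ICC 0) to 0.009 (ICC 0.01) at 3% risk.
2. Limit the primary conclusion to unit-level risk and make no non-inferiority claim for colonised infants. Reword the interpretation in SAP 9.3 to say that the risk is not higher by 5 percentage points or more, and report the confidence interval and the implied relative risk.
3. Justify 0.05 for the all-infant risk against a 3% control risk, or tighten it on clinical grounds. Purely as an illustration, a margin of 0.025 would have power Φ(0.025 / 0.00897 − 1.645) = 87% at 3% control risk and 64% at 6% (SE 0.0125), both at ICC 0.01. The documents give no clinical basis for that value, and it would still admit a ratio of up to 5.5/3 = 1.83.
4. Add a descriptive analysis in colonised infants only if Gram-negative bloodstream infection counts among them can be obtained. The variables listed in SAP section 5 do not include such a count. State that colonisation arises after randomisation and may itself be affected by the regimen.

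Items 1 and 2 cost wording and one change of denominator. The price is a narrower conclusion and the loss of the stated size and power. A tighter margin under item 3 would also lower power.
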